## Methods

### Aims

The primary aim of this study is to describe global 30-day postoperative mortality rates for patients undergoing a trauma laparotomy.

The secondary aims of the study are as follows:

To describe the epidemiological characteristics (demographics, injury characteristics, baseline clinical characteristics and surgical casemix) for patients undergoing a trauma laparotomy.To describe the preoperative, perioperative and postoperative processes of care for patients undergoing a trauma laparotomy.

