### Patient criteria

We will include patients of all ages who present to hospital with a blunt or penetrating injury and undergo a trauma laparotomy within 5 days of presentation to the treating centre (day 0 being time of presentation). A patient will be included for final analysis if >70% of the data points required have been recorded.

Exclusion criteria are as follows:

Patients undergoing a laparotomy ≥5 days (ie, 120 hours) since presentation to the treating centre.Any relook laparotomy, including transfers from another centre for further and/or definitive surgery.Any laparoscopic (including laparoscopic converted to open), robotic, or image-guided procedures.Patients who have been recently discharged from any hospital (including for non-trauma-related admissions) and have represented within 30 days of discharge.

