### Statistical analysis

A formal statistical analysis plan will be produced. However, in brief, participating centres will be stratified based on their country into groups based on their Human Development Index (HDI) rank, with 30-day mortality then reported for each HDI group. Further analyses will include stratification against other economic and health indices, and multivariable logistic modelling will be used to investigate primary and secondary study aims.

As there are a lack of data on trauma laparotomy globally, performing an accurate sample size calculation is not feasible. Data suggest that 30-day mortality rates following trauma laparotomy in high-income countries (HICs) are around 9%^3^ and in low-income and miffle-income countries (LMICs) are around 17%^17–19^; using an alpha value=0.05 and power=80%, to show a difference between HIC and LMIC settings, a total of 552 patients are required to be recruited to the study. Based on data from other observational studies,^3 7 8^ we would expect over a 30-day observation period each centre to commit around 3–5 patients to the study. Therefore, with around 150 recruiting centres from our pre-existing research network, we would expect to meet the sample size required.

Missing values are to be expected in a study of this kind and will potentially affect certain centres more than others. To allow for potential imputation without introducing significant bias, we will include patients with ≥70% completeness. Multiple imputation methods will be used for the remaining missing data.

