## Discussion

We present the protocol for a global observational multicentre study, the GOAL-Trauma study, which aims to evaluate the patient and injury factors in those undergoing a trauma laparotomy and to assess any variation observed in outcomes occurring globally. This study will provide a global snapshot of the current 30-day mortality rates following trauma laparotomy, as well as insight into any variation observed in the time delays for receiving trauma care, the disease and patient factors present and patient outcomes.

There remains a relative paucity of evidence regarding global outcomes following trauma laparotomy. Much of the current data on trauma laparotomy derives from the military setting, and the remaining civilian-level data currently published predominantly comes from high-income settings. Without high-quality data available, ensuring a greater awareness and development towards global trauma strategies is challenging. Trauma laparotomy is a vital procedure in trauma care, therefore this study will provide key insights into trauma management.

Trauma care is complex, with heterogeneous patient groups and disease presentations, set within varying macrohealthcare and microclinical requirements.^21^ This study will collect data across the patient journey, allowing key parts and limitations within this complex journey of trauma care to be identified and unpicked. However, data collection methods can often be challenging in LMIC settings, as robust numerical data may not be readily available, limiting conventional analysis techniques. We will use the Abbreviated Injury Scale (AIS) to categorise the wide spectrum and severity of traumatic injuries sustained,^22^ with the individual AIS scores further used to calculate an Injury Severity Score for each patient, quantifying overall injury burden and will be adjusted for in the final data analysis.

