As with any trauma study, there remains a large selection bias, as there will be many unaccounted mortalities from trauma that did not make it to hospital, did not make it into theatre, or deemed not appropriate for surgery, therefore not included in the study. We also suspect there may be a relatively high amount of missing data, however we will attempt to adjust for this with multiple imputation methods. Of further note, we are not including patients who have undergone any laparoscopic procedure (including laparoscopic converted to open), alongside any robotic procedures or interventional radiology procedures, to ensure the core data set provides the clearest picture on trauma provision and pathways globally.

The GOAL-Trauma study will provide high-quality observational multicentre data on an important topic in trauma care globally, using the trauma laparotomy as a surrogate marker. Identifying the key aspects of patient and injury factors in this patient cohort, both prehospital and in-hospital, will ensure the primary data required to understand barriers and key target areas to improve overall care and outcomes.

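### Dropping patients below 70% record completeness, even when their outcome is known, may bias the primary mortality estimate, and the cut-off is stated in two ways

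*Protocol article*

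**What the plan says.** The primary aim is descriptive: "The primary aim of this study is to describe global 30-day postoperative mortality rates for patients undergoing a trauma laparotomy" (Aims). Under Statistical analysis, centres are grouped by the Human Development Index (HDI) of their country, "with 30-day mortality then reported for each HDI group".

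The completeness rule appears twice:
- Patient criteria: "A patient will be included for final analysis if >70% of the data points required have been recorded".
- Statistical analysis: "To allow for potential imputation without introducing significant bias, we will include patients with ≥70% completeness". The next sentence adds: "Multiple imputation methods will be used for the remaining missing data".

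On the missing data it expects, the article says:
- "Missing values are to be expected in a study of this kind and will potentially affect certain centres more than others" (Statistical analysis).
- "We also suspect there may be a relatively high amount of missing data" (Discussion).
- "data collection methods can often be challenging in LMIC settings, as robust numerical data may not be readily available" (Discussion).

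No exemption is given for a patient whose outcome is recorded but whose other fields are sparse.

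**The concern.** The rule selects patients on something that happens after enrolment, namely how much was written down about them. A mortality proportion survives such selection only if completeness is unrelated to death and, for a pooled rate, unrelated to settings with different mortality. The article's own remarks undercut the second condition and give no assurance on the first.

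An unadjusted mortality rate by HDI group needs the outcome and the country. A sparse record on imaging or process of care is no reason to discard a patient whose outcome is known. Multiple imputation, which the Discussion offers as the adjustment for missing data, cannot help, because these patients have left the data set before it starts.

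At stake are the pooled global rate, the HDI-group rates and the contrast between them. The patients most at risk of removal come from the settings where the Discussion says published civilian data are scarcest.

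**Working it through.** **1. The two cut-offs.** More than 70% (Patient criteria) and at least 70% (Statistical analysis) differ only for records at exactly 70%. The numerical effect is small, but the two cannot both be applied.

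**2. The plan's own sample size.** Inputs from Statistical analysis: 9% mortality in high-income countries (HIC), 17% in LMIC, alpha 0.05, power 80%, total 552. Assumed here: two-sided test, equal groups, pooled variance, no continuity correction. With a mean proportion of 0.13:

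n per group = [1.96·√(2·0.13·0.87) + 0.8416·√(0.09·0.91 + 0.17·0.83)]² / 0.08² = (0.932 + 0.397)² / 0.0064 ≈ 276.2

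Rounded up this is 277 per group, 554 in total. At 276 per group (552) power is 79.97%. The stated figure reproduces, so there is no sample-size error.

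**3. Effect of exclusion on an observed rate.** Let p be true mortality, d the share of deaths excluded and s the share of survivors excluded:

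observed = p(1−d) / [p(1−d) + (1−p)(1−s)]

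The documents give neither d nor s, so both are assumed. Example for p = 17%, s = 10%, d = 20%: 0.136 / (0.136 + 0.747) = 15.4%.

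| s / d (assumed) | true 17% observed as | true 9% observed as |
|---|---|---|
| 5% / 5% | 17.0% | 9.0% |
| 5% / 10% | 16.3% | 8.6% |
| 5% / 20% | 14.7% | 7.7% |
| 10% / 20% | 15.4% | 8.1% |
| 10% / 30% | 13.7% | 7.1% |
| 10% / 5% (reversed) | 17.8% | 9.5% |

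The bias is nil when d = s, downward when d > s and upward when d < s.

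**4. Effect on the HIC–LMIC contrast**, starting from 276 per group and 8.0 points:
- Only LMIC affected, s/d = 5%/10%: 16.25 − 9 = 7.25 points, power about 72%.
- Only LMIC affected, 10%/20%: 6.4 points, power about 61%.
- Only LMIC affected, 10%/30%: 4.7 points, power about 40%.
- Equal loss within each group (LMIC 10%/10%, HIC 5%/5%): 8.0 points, power about 77%.
- Reversed in LMIC (10%/5%), HIC 5%/5%: 8.8 points, power about 83%.

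**5. Loss by setting only, unrelated to death.** Suppose 20% of LMIC and 5% of HIC patients are lost from a half-and-half cohort. The pooled rate goes from 13.0% to (0.5·0.80·0.17 + 0.5·0.95·0.09) / (0.5·0.80 + 0.5·0.95) = 0.11075 / 0.875 = 12.7%. The two group rates do not move, but the global rate does.

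**6. Lost numbers alone.** With 5%, 10% or 20% excluded in both groups regardless of outcome, power is 78%, 76% or 71%. Keeping 552 analysed would need 552/0.95 = 582, 552/0.90 = 614 or 552/0.80 = 690 recruited. The 552 is stated as the number to recruit, with no allowance for exclusions.

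**The case against.** A reader might infer that the rule removes deaths selectively and that mortality will therefore be understated. The documents do not support that. No section links death to incomplete records; they speak only of differences between centres and of LMIC settings. It is plausible that a patient who dies in theatre leaves a thin postoperative record, but the list of required fields is in a supplementary table not shown here. If postoperative fields are not required after death, most of that mechanism disappears. The neutral and reversed rows above show that the direction is open. This part of the objection stands.

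It is also fair that covariate completeness matters to part of the primary analysis: Statistical analysis plans multivariable logistic models for the primary aim, and the Discussion plans adjustment for injury severity. But imputing covariates in those models meets that need without dropping patients from a descriptive rate.

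The power figures are secondary. The aim is descriptive, the article itself says an accurate sample size calculation is not feasible, and its expected yield of 150 centres at 3 to 5 patients is 450 to 750, which spans 552.

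Finally, a careless remedy could do harm. Under Study design follow-up ends at discharge, and Data collection allows no patient contact. Limiting the analysis to patients with status known at day 30 would keep in-hospital deaths and drop many early-discharged survivors, which would inflate mortality. This also stands and shapes the fix.

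The objection does not rescue the rule. A formal analysis plan is still to be produced, but the protocol already fixes who is analysed and gives avoidance of bias as the reason.

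**Conclusion.** The concern holds in a conditional form. Two things are certain from the text: the threshold is stated inconsistently, and eligible patients with a recorded outcome can be excluded from the primary estimate and never reached by imputation. Given the missingness the article itself expects, this may remove patients selectively by centre and setting, and possibly by outcome. The stated rationale is therefore not supported.

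Size and direction cannot be determined from the documents. Under the assumed shares a true 17% would be observed anywhere from 13.7% to 17.8%, and a true 9% from 7.1% to 9.5%, with no bias if deaths and survivors are lost equally within a group. That lower-HDI centres would lose most is a reasonable reading of the Discussion, not something the article states. The contrast and power figures also assume equal groups, which the article does not specify.

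**What to change.** - Remove completeness as a condition for the primary mortality estimate. Include every eligible patient whose outcome is recorded at the protocol's end of follow-up: died, discharged alive, or alive in hospital at day 30. Survivors discharged before day 30 are then kept.
- Use multiple imputation for missing covariates in the multivariable models.
- Keep a completeness-restricted set only as a sensitivity analysis, with one threshold used in both Patient criteria and Statistical analysis.
- Report the number of below-threshold patients by outcome and by HDI group, so that readers can see whether the loss is selective.
- Delete or reword the statement that the cut-off avoids significant bias.

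The cost is a change of wording in the protocol and analysis plan, more imputed covariate values in the adjusted models, and one extra sensitivity run. No new data are needed provided below-threshold records are retained in the database. Ethical approval says no amendments are planned, so the change should be documented before the analysis.

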### Ethical approval

The study has received ethics approval from the Cambridge Psychology Research Ethics Committee PRE.2023119). According to the UK National Health Service Health Research Authority tool (https://www.hra-decisiontools.org.uk/research/), the study can be considered locally as a clinical evaluation study in the UK. Outside of the UK, each centre’s local team will be responsible for obtaining the necessary local approvals in line with their hospital and/or national regulations. Collaborators will need to confirm local approval has been granted prior to of uploading patient data.

The study has been pre-registered to ClinicalTrials.gov (NCT06180668) and will be reported following the Strengthening the Reporting of Observational Studies in Epidemiology statement guidelines and checklists.^20^ The sponsor of the study will be the University of Cambridge, with support provided from a number of collaborators. Once complete, data and conclusions from the study will be disseminated through the research network to all collaborators, with all work from the study planned to be published in open-access journals. As an observational study, no future amendments to the protocol are planned.

### Patient and public involvement

Patient and public involvement (PPI) groups were involved in the development of the study protocol and key participant literature. During the protocol development stage, a PPI discussion group was convened, involving with people who have specific lived experiences relevant to the project; feedback obtained from this session directly influenced aspects of methodology and proposed outcomes for the study. A separate PPI group further reviewed the proposed patient-focused literature associated with the study, providing comments and edits to this work that were implemented in the eventual patient information sheets produced.

## Discussion

We present the protocol for a global observational multicentre study, the GOAL-Trauma study, which aims to evaluate the patient and injury factors in those undergoing a trauma laparotomy and to assess any variation observed in outcomes occurring globally. This study will provide a global snapshot of the current 30-day mortality rates following trauma laparotomy, as well as insight into any variation observed in the time delays for receiving trauma care, the disease and patient factors present and patient outcomes.

There remains a relative paucity of evidence regarding global outcomes following trauma laparotomy. Much of the current data on trauma laparotomy derives from the military setting, and the remaining civilian-level data currently published predominantly comes from high-income settings. Without high-quality data available, ensuring a greater awareness and development towards global trauma strategies is challenging. Trauma laparotomy is a vital procedure in trauma care, therefore this study will provide key insights into trauma management.

Trauma care is complex, with heterogeneous patient groups and disease presentations, set within varying macrohealthcare and microclinical requirements.^21^ This study will collect data across the patient journey, allowing key parts and limitations within this complex journey of trauma care to be identified and unpicked. However, data collection methods can often be challenging in LMIC settings, as robust numerical data may not be readily available, limiting conventional analysis techniques. We will use the Abbreviated Injury Scale (AIS) to categorise the wide spectrum and severity of traumatic injuries sustained,^22^ with the individual AIS scores further used to calculate an Injury Severity Score for each patient, quantifying overall injury burden and will be adjusted for in the final data analysis.

As with any trauma study, there remains a large selection bias, as there will be many unaccounted mortalities from trauma that did not make it to hospital, did not make it into theatre, or deemed not appropriate for surgery, therefore not included in the study. We also suspect there may be a relatively high amount of missing data, however we will attempt to adjust for this with multiple imputation methods. Of further note, we are not including patients who have undergone any laparoscopic procedure (including laparoscopic converted to open), alongside any robotic procedures or interventional radiology procedures, to ensure the core data set provides the clearest picture on trauma provision and pathways globally.

The GOAL-Trauma study will provide high-quality observational multicentre data on an important topic in trauma care globally, using the trauma laparotomy as a surrogate marker. Identifying the key aspects of patient and injury factors in this patient cohort, both prehospital and in-hospital, will ensure the primary data required to understand barriers and key target areas to improve overall care and outcomes.
